## Abstract

Many studies have supported the positive effects of an active lifestyle on the prevention and treatment of pregnancy-related complications, as well as maintaining fitness and functionality. The COVID-19 pandemic has underscored the need for virtual approaches to health interventions; however, few studies have examined the effectiveness of these interventions. The Standard Protocol Items: Recommendations for Interventional Trials 2025 guidelines were followed to describe the protocol of the ACTIVE PREGNANCY trial, an intervention study that delivers a physical exercise programme in-person (IN) and online (ON) to improve maternal physical activity (PA), fitness and healthy lifestyle parameters in pregnant women. Pregnant women will be invited to participate in a multisite, multicomponent exercise programme delivered either IN or ON by qualified exercise physiologists. Both groups will receive an exercise intervention delivered in different real-life environments. Participants will undergo basic fitness field tests and complete questionnaires assessing PA, fitness and lifestyle parameters before starting the exercise programme and after completing 12 weeks of the intervention. Researchers will test whether the intervention is beneficial in maintaining or improving maternal parameters after 12 weeks and will compare the effectiveness of different exercise modes. Subgroups of maternal age and weekly volume of PA will also be analysed.

Primary outcomes: PA volume and health-related and functional fitness. Secondary outcomes: healthy lifestyle parameters. Additional outcomes: satisfaction with the exercise interventions and resources. This study was approved by the Ethics Committee of Santarém Polytechnic University and registered on ClinicalTrials.gov (NCT06954454). Findings will be disseminated via publications, conferences and training programmes.

WHAT IS ALREADY KNOWN ON THIS TOPICExercise during pregnancy provides various benefits for maternal health and cardiorespiratory fitness.The impact of exercise on the other health-related and skill-related fitness components is poorly explored.The effectiveness of supervised virtual interventions is poorly understood.WHAT THIS STUDY ADDSThis is the first study addressing the effectiveness of virtual intervention with pregnant women.The study will provide novel insights regarding the main maternal fitness components.The study covers a comprehensive analysis of health-related and skill-related fitness components.HOW THIS STUDY MIGHT AFFECT RESEARCH, PRACTICE OR POLICYThe results of the present work will be useful to test and compare the effectiveness of the in-person and online exercise programmes on maternal health and fitness during pregnancy.The findings will provide support to healthcare professionals in promoting physical activity and exercise during pregnancy and to exercise professionals in delivering safe and effective programmes.The results will inform future exercise recommendations and practice regarding virtual training.The results will inform public health strategies for promoting active and healthy lifestyles during pregnancy regardless of maternal age, health status and fitness levels.This study could pave the way for targeted interventions incorporating prenatal exercise as a prevention strategy of pregnancy-related complications by promoting an active and healthy lifestyle.

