We hypothesised that a multicomponent supervised prenatal physical exercise programme previously described in Santos-Rocha *et al*’s study^14^ positively impacts PA, fitness, lifestyle and health parameters of women throughout pregnancy, regardless of the delivery environment (in-person (IN) *vs* online (ON)), maternal age or weekly volume of PA, and that both exercise environments are equally effective.

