### Objectives

To describe the study protocol of the ACTIVE PREGNANCY trial following the updated Standard Protocol Items: Recommendations for Interventional Trials 2025 guidelines,^15^ which is a supervised multicomponent prenatal exercise programme delivered either IN or ON aimed at improving maternal PA levels, health-related and functional fitness, healthy lifestyle and health parameters throughout pregnancy, regardless of maternal age or baseline PA. The primary objectives are to compare the impact of IN *versus* ON interventions on PA levels, self-perceived fitness and health-related and functional fitness. The secondary objectives are to assess the impact of both interventions on lifestyle (ie, Mediterranean diet, sleep quality, happiness and depression) and health parameters (ie, weight gain, gestational diabetes or hypertension) and to analyse differences by maternal age subgroups (<35 *vs* 35+years) and weekly volume of PA (<150, 150–300 or 300+min/week). Additional objectives include exploring participant satisfaction with the exercise interventions and evaluating the usefulness of digital resources (ie, ACTIVE PREGNANCY Guide, YouTube channel ACTIVE PREGNANCY and the framework of the ACTIVE PREGNANCY app).

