### Trial design

This is a multicentre, two-arm, parallel-group, randomised controlled trial (RCT) with a 1:1 allocation ratio and an equivalence framework. Pregnant women will be randomly assigned to either an IN or ON supervised multicomponent exercise intervention.

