### Sample size

The sample size was determined using G*Power software (V.3.1) based on previous studies. To detect statistical differences between pre- and postdifferences in one group, a sample of 36 pregnant women was considered based on calculations performed using G*Power with the inputs of the mean±SD from previous studies by Dennis *et al*,^19^ a power of 0.8 and α≤0.05. Additionally, to detect statistical differences between two independent groups of pregnant women included (experimental) or not (control) in exercise programmes, a sample size of 59 per group was calculated based on the mean±SD values from previous studies by Ramírez-Vélez *et al*,^20^ a power of 0.8 and α≤0.05. Based on an expected loss-to-follow-up rate of 20%, we plan to include 100 participants in each of the two intervention groups. Therefore, a total of 200 pregnant women will be recruited and randomly allocated to either the IN or ON group (100 per group).

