### Statistical methods for primary and secondary outcomes

Demographic data (age, weight, gestational age, area of residence and date of birth) will be described using frequencies and percentages for categorical variables.

Descriptive statistics (mean, SD, median and IQR) will be used to summarise baseline characteristics of participants in both groups (IN and ON).

Descriptive and inferential statistics will be applied to all outcomes.

A comparative analysis of IN *versus* ON interventions will be conducted using both intention-to-treat and per-protocol approaches. Comparative analysis will be used to compare changes in primary and secondary outcomes between IN and ON groups over time (baseline and postintervention). Subgroup analyses will evaluate potential differences between maternal age groups (<35 *vs* 35+ years) and PA level groups.

Adherence to the intervention (proportion of attendance in the planned sessions) will be calculated after the postintervention assessments.

Data from participants who do not complete at least 80% of the scheduled sessions will be considered a loss to follow-up.

Regarding additional outcome analysis, the evaluation of interventions and resources will be performed through descriptive analysis, summarising satisfaction with resources and exercise interventions.

Continuous variables will be assessed for normality using Shapiro–Wilk tests. Normally distributed variables will be presented as mean±SD and analysed using the independent sample t-test. The non-normally distributed data will be reported as the median with IQR and will be analysed using the Mann–Whitney test. For the within-group difference, normally distributed variables will be calculated with the paired-sample t-test. In contrast, those non-normally distributed variables will be calculated with the paired-sample non-parametric Wilcoxon test. Categorical data will be analysed using Pearson’s χ^2^ test or Fisher’s exact test, as appropriate.

A significance level of 0.05 (alpha level) will be set for all statistical tests. Power calculations were performed to ensure that the study was adequately powered to detect clinically significant differences between groups. All statistical analyses will be conducted in Statistical Package for the Social Sciences.

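### Within-arm before-after tests in two exercising arms cannot show that the programme itself is beneficial; the randomised in-person versus online comparison is unaffected

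*Protocol article*

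**What the plan says.** The protocol article asks two different questions.

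- **IN versus ON.** The Objectives make this comparison primary, and Trial design describes a two-arm randomised trial "with a 1:1 allocation ratio and an equivalence framework".
- **Is the programme itself beneficial?** The Abstract states "Researchers will test whether the intervention is beneficial in maintaining or improving maternal parameters after 12 weeks". The hypothesis that closes Background and rationale is that the programme "positively impacts PA, fitness, lifestyle and health parameters of women throughout pregnancy, regardless of the delivery environment", and it adds equal effectiveness of the two settings as a further claim. In the Objectives, "The secondary objectives are to assess the impact of both interventions on lifestyle" and health parameters. The key-messages box after the Abstract and the Discussion also speak of testing, or giving evidence on, the programmes' effectiveness.

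On design, the Abstract says "Both groups will receive an exercise intervention delivered in different real-life environments". Table 1 gives both arms the same type, frequency, duration and intensity of exercise; supervision mode and setting differ. There is no non-exercise or usual-care arm.

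On analysis, Statistical methods says "For the within-group difference, normally distributed variables will be calculated with the paired-sample t-test", with the Wilcoxon test for non-normal data and a 0.05 level for every test. Sample size includes a matching calculation: "To detect statistical differences between pre- and postdifferences in one group, a sample of 36 pregnant women was considered".

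**The concern.** Randomisation supports one causal contrast, IN against ON. It gives no information on what would have happened to these women without the programme. The benefit question needs that information, and the only planned analysis that bears on it is each arm's change from its own baseline. In this population, before-after change is a poor stand-in, because pregnancy advances by the same 12 weeks over which the programme is delivered. Among the listed outcomes, weight gain and pregnancy-related symptoms are bound up with gestation itself.

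At stake is what the trial may conclude about effectiveness, which the Discussion wants to carry into prescription guidelines and policy. The error can run either way. Change due to gestation can look like benefit, or it can hide a real one. Limitations of the study covers measurement methods, device cost and assessment burden, but not the missing comparator.

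**Working it through.** **Inputs from the protocol article**

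- Baseline at 13–20 and follow-up at 25–32 gestational weeks (Timeline): 25 − 13 = 12 and 32 − 20 = 12. Programme length is also 12 weeks (Table 1).
- Other organised exercise or sport is permitted during the trial (Concomitant care).
- 100 per arm with 20% expected loss (Sample size): 100 × 0.80 = 80 completers per arm.
- Level 0.05 (Statistical methods), taken here as two-sided.

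**Assumption.** The article gives no size for gestational drift and no SD of change. Drift is therefore set at a range of values, in units of the SD of the change score.

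**1. The plan's own figure.** The one-group n of 36 cannot be reproduced forwards, because the mean and SD behind it are not in the article. Solved backwards at 80% power, it corresponds to a standardised change of about 0.48 (two-sided) or 0.42 (one-sided). It is powered for any change from baseline, whatever the cause.

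**2. What each analysis estimates.** Let g be the average change from advancing pregnancy and outside exercise, and let b(IN) and b(ON) be the programme effects.

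- Within-arm change: b(IN) + g, or b(ON) + g.
- Between-arm difference: [b(IN) + g] − [b(ON) + g] = b(IN) − b(ON).

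The paired test has as its null hypothesis b + g = 0, not b = 0. Every woman is exposed to the programme over the same weeks as g accrues, so the two cannot be separated. In the between-arm difference, a g common to both arms cancels.

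**3. Size of the problem when b = 0.** The paired t-test has n − 1 = 79 degrees of freedom and noncentrality (drift) × √80:

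| Assumed drift (SD of change) | Noncentrality | P(p<0.05), one arm, one outcome |
|---|---|---|
| 0 | 0 | 5.0% |
| 0.2 | 1.79 | 42.4% |
| 0.3 | 2.68 | 75.5% |
| 0.4 | 3.58 | 94.2% |

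At 80% power, the change this test detects is 0.317 SD.

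**4. Simulation** (20,000 trials, 80 per arm, no programme effect, drift common to both arms):

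| Drift | One arm significant | Both arms significant | IN–ON test significant |
|---|---|---|---|
| 0 | 5% | 0.2% | 5% |
| 0.2 | 43% | 19% | 5% |
| 0.3 | 76% | 57% | 5% |
| 0.5 | 99% | 99% | 5% |

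**5. The opposite error.** With a true benefit of +0.3 SD and a drift of −0.3 SD, b + g = 0 and the paired test is significant in only 5% of trials. The programme would have worked and the analysis would show no change.

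**6. Maintenance and equivalence.** A non-significant paired test does not show that a parameter was maintained, since it is not a test for absence of change. Showing b(IN) close to b(ON) leaves open that both are zero.

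**The case against.** The strongest reply is that this is not the trial's main question. The primary objectives compare IN with ON, and the Discussion gives that comparison as the main purpose. This stands. A reader might infer that gestational change undermines the trial's principal result, but steps 2 and 4 show that shared drift leaves the randomised comparison unbiased.

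Second, Statistical methods does not say that the paired tests decide benefit, and it gives no rule for calling a parameter maintained or improved. This also stands in part. A reader might infer that significant rises will be reported as improvement and non-significant falls as maintenance; the article describes no such reporting. What remains is that a test of benefit is promised and no other stated analysis could supply it.

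Third, the percentages are simply paired-test power at chosen effect sizes. That is correct: they illustrate the scale and do not predict it. A practice effect in the field tests is conceivable too, but the article gives nothing on it and the argument does not need it.

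Fourth, the n of 36 does not set enrolment: 36/0.80 = 45, and the other calculation, 59 per group, is already larger. So the 100 per arm should not be read as resting on the pre-post calculation.

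Fifth, a separate analysis plan may exist. It could relabel these analyses, but it cannot supply a comparator that the design lacks. Prior evidence does not fill the gap either: the key-messages box calls the effect on fitness components other than cardiorespiratory fitness poorly explored, and that of supervised virtual programmes poorly understood.

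**Conclusion.** The point holds for the benefit question only. The article promises to test whether the programme is beneficial, and the only stated analysis that addresses this confounds the programme with 12 weeks of advancing pregnancy and any outside exercise. It can show neither benefit when significant nor maintenance when not, and equivalence of the arms would not show benefit.

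This conclusion follows from the design and needs no assumed number. Its practical size does: with no programme effect and 80 completers per arm, drift of 0.2, 0.3 or 0.4 SD of change gives p<0.05 in 42%, 76% or 94% of trials per outcome, assuming normal change scores and a two-sided 0.05 level.

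The documents do not support the stronger reading that the trial as a whole fails to answer its question.

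**What to change.** 1. **Statistical methods:** report within-arm change as mean change with 95% CI, labelled descriptive and not attributed to the programme. The label is what matters, because an interval that excludes zero carries the same information as p<0.05.
2. **Conclusions:** limit confirmatory statements to the randomised IN–ON difference.
3. **Wording:** bring the benefit and effectiveness statements into line in the Abstract, the key-messages box, the hypothesis in Background and rationale, the Objectives and the Discussion.
4. **Limitations of the study:** state that there is no non-exercise comparator, so change over time cannot be ascribed to the programme and equivalence would not show benefit.

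No visit, measurement or enrolment figure changes. The cost is the effectiveness claim, which the design cannot support. Because this narrows a stated hypothesis and a secondary objective after the May 2025 start of recruitment, it should be recorded as a dated amendment.

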## Introduction

### Background and rationale

 Many studies have been supporting the positive effects of an active lifestyle concerning the prevention and treatment of pregnancy-related complications, such as gestational diabetes, hypertension, obesity, low back pain, urinary incontinence and depression, as well as regarding its effectiveness in maintaining fitness and functionality and improving postpartum recovery. Therefore, maternal physical activity (PA) is a significant public health issue.^1^ On the other hand, physical fitness is considered a powerful marker of health, as it is associated with a lower risk of cardiovascular events, cancer and all-cause mortality across all ages.^2 3^ Moreover, some studies with pregnant women have highlighted the potential impact of higher physical fitness levels on improved maternal and foetal health.^4^,^6^

Practice guidelines have become increasingly popular tools for synthesising evidence-based information to assist practitioners and patients in making decisions related to starting or continuing PA. Updated guidelines for exercising during pregnancy have been issued in recent years^7^,^9^ to facilitate informed advice from healthcare providers. Despite this knowledge, most women still do not receive proper guidance on how to exercise during pregnancy or after childbirth, and the prevalence of physical inactivity is still high among pregnant women.

The isolation periods during the COVID-19 pandemic may have harmed the health and fitness of pregnant women and introduced various PA dilemmas by experiencing disruption in their access to obstetric healthcare.^10^ This pandemic has accentuated the need for virtual interaction with populations considered to be at greater risk, such as pregnant women.^11^ Virtual interaction has increased worldwide, and its advantage is that it enables reaching remote and excluded populations, emphasising online programme delivery. Few studies have been conducted so far showing positive effects on selected pregnancy outcomes, such as birth weight and depression,^12 13^ but there is a lack of studies supporting the effectiveness of virtual interactions on general health and fitness. Moreover, the relative efficacy of these interventions on fitness parameters has not been compared in different environments.

We hypothesised that a multicomponent supervised prenatal physical exercise programme previously described in Santos-Rocha *et al*’s study^14^ positively impacts PA, fitness, lifestyle and health parameters of women throughout pregnancy, regardless of the delivery environment (in-person (IN) *vs* online (ON)), maternal age or weekly volume of PA, and that both exercise environments are equally effective.

### Objectives

To describe the study protocol of the ACTIVE PREGNANCY trial following the updated Standard Protocol Items: Recommendations for Interventional Trials 2025 guidelines,^15^ which is a supervised multicomponent prenatal exercise programme delivered either IN or ON aimed at improving maternal PA levels, health-related and functional fitness, healthy lifestyle and health parameters throughout pregnancy, regardless of maternal age or baseline PA. The primary objectives are to compare the impact of IN *versus* ON interventions on PA levels, self-perceived fitness and health-related and functional fitness. The secondary objectives are to assess the impact of both interventions on lifestyle (ie, Mediterranean diet, sleep quality, happiness and depression) and health parameters (ie, weight gain, gestational diabetes or hypertension) and to analyse differences by maternal age subgroups (<35 *vs* 35+years) and weekly volume of PA (<150, 150–300 or 300+min/week). Additional objectives include exploring participant satisfaction with the exercise interventions and evaluating the usefulness of digital resources (ie, ACTIVE PREGNANCY Guide, YouTube channel ACTIVE PREGNANCY and the framework of the ACTIVE PREGNANCY app).

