### Outcomes

Primary, secondary and additional outcome measures, including the specific measurement variables, timeframe and instruments, are shown in table 2.

**Table 2 T2:** Primary, secondary and additional outcome measures, including the specific measurement variables, timeframe and instruments

Outcome measures	Instruments
Primary outcome measuresTimeframe: baseline (week 0) and after 12-week intervention (weeks 13 and 14)Analysis metric: change from baseline	
PA level and pattern of PA in the type of PA (work, active commuting, exercise, etc.), type of exercise, duration of each session (time spent in PA), weekly frequency and intensity and weekly volume (MET-min/week).	PPAQ^21^ and get active questionnaire for pregnancy^22^
Self-perceived fitness: self-perceived global fitness and fitness components (cardiorespiratory, strength, speed/agility and flexibility) when compared with other women of the same age. Likert scale 1 (poor) to 5 (very good).	IFIS^23^
Cardiorespiratory fitness estimated in mL/kg/min	Cardiorespiratory fitness—6-min walk test (average distance covered in metres and estimated cardiorespiratory fitness in mL/kg/min)^24^https://youtu.be/CUaFgfdSObc
Upper limbs strength	Upper limb strength—wall push-ups (number of repetitions in 30 s)^6 17^https://youtu.be/dp_tRoyxVYU
Lower limbs strength	Lower limb strength—sit-and-stand (number of repetitions in 30 s)^6 17 25^https://youtu.be/3ihcqnzyTXk
Dynamic balance	Dynamic balance—superwoman^6 17^https://youtu.be/Xiv_vWpe4-A
Static balance	Static balance—one-leg stance^6 17^https://youtu.be/sr0eYCfbLiM
Lower limbs flexibility	Lower limbs flexibility—modified sit and reach (mm)^6 17^https://youtu.be/Y6y_FAa3ulk
Upper limbs flexibility	Upper limbs flexibility—back scratch (mm)^6 17^https://youtu.be/MBwKi8kSFx8
Agility	Agility—time up and go over 3-m distance (in min)^6 17^https://youtu.be/3C944cMuTFo
Secondary outcome measuresTimeframe: baseline (week 0) and after 12-week intervention (weeks 13 and 14)Analysis metric: change from baseline	
Sleep quality	PSQI^26^
Weight prepregnancy, weight at baseline and weight gain (kg)	Body weight: measure with the participant wearing light clothing and without shoes^27^
Happiness scale	SHS^28^
Depression scale	EPDS^29^
Adherence to the Mediterranean diet	MEDAS^30^
HR	Measured rest HR, estimated maximal HR and calculated target HR (beats per minute)

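### Comparing change in weekly PA across baseline-PA groups, which the plan leaves open, would produce a gradient by regression to the mean even if the programme effect is nil or uniform

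*Protocol article*

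**What the plan says.** All references are to the protocol article.

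- **Objectives** lists, among the secondary objectives, an analysis of differences by maternal age and by "weekly volume of PA (<150, 150–300 or 300+min/week"). The clause gives no time point, but the aim in the same section is improvement "regardless of maternal age or baseline PA".
- **Background and rationale** ends with the hypothesis of a positive impact whatever the delivery environment, "maternal age or weekly volume of PA, and that both exercise environments are equally effective".
- **Outcomes, Table 2** puts PA first among the primary outcomes, covering session duration, "weekly frequency and intensity and weekly volume (MET-min/week"). The block header reads "Analysis metric: change from baseline".
- **Statistical methods for primary and secondary outcomes** states: "Subgroup analyses will evaluate potential differences between maternal age groups (<35 *vs* 35+ years) and PA level groups". The tests named are unadjusted: an independent-sample t-test or Mann–Whitney test between groups, and for pre-post change, "For the within-group difference, normally distributed variables will be calculated with the paired-sample t-test" (Wilcoxon otherwise). No baseline covariate is named.
- **Trial design**: both arms receive the exercise programme, so there is no untreated arm.

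**The concern.** A woman's baseline PA would decide which group she is in, and the same or a closely related baseline value is subtracted to form her outcome. PA is self-reported by questionnaire (Limitations of the study), so the baseline contains reporting error and week-to-week variation. Women who happen to report low fall in the lowest group and tend to rise at week 12. Women who happen to report high fall in the highest group and tend to drop. This needs no programme effect.

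What is at stake is the hypothesis that benefit does not depend on weekly PA. Comparing PA change across the PA-level groups would tend to reject it for a purely statistical reason. The trial could then report that the programme mainly helps inactive women when its effect is the same for everyone, or nil. Pre-post tests within a PA group have the same fault, and no untreated arm exists to show how much change to expect without the programme.

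**Working it through.** The plan gives no figure to reproduce, so the check asks what the analysis yields when there is nothing to find.

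**Inputs from the article.** Cut-offs of 150 and 300 min/week; α = 0.05; 200 women with 20% expected loss, so 200 × (1 − 0.2) = 160 analysed.

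**Assumptions (not in the article).** Mean and SD of weekly PA, and the correlation r between baseline and week 12. Base case: normal, mean 225, SD 150 min/week, r from 0.5 to 0.9.

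**Step 1: direction.** With no true change and equal variances, the expected change given baseline Y₁ is −(1 − r)(Y₁ − μ). The lowest group's mean lies below μ and the highest group's above it. For any r < 1 the first therefore gains and the second loses, whatever the mean and SD.

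**Step 2: size.** The lower cut-off is (150 − 225)/150 = −0.5 SD. The mean of a normal variable below −0.5 SD is −0.352/0.309 = −1.14 SD. At r = 0.5 the expected change is therefore 0.5 × 1.14 × 150 ≈ +86 min/week. The upper cut-off is symmetric. Simulated mean change under no effect:

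| r | <150 | 300+ |
|---|---|---|
| 0.5 | +86 | −86 |
| 0.7 | +51 | −52 |
| 0.9 | +17 | −17 |

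A skewed distribution (lognormal, median 200, log-SD 0.7) gives +68/−126, +38/−77 and +12/−25.

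**Step 3: false-positive rates** (4,000 simulated trials per setting, N = 160, no effect, one variable for grouping and outcome):

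| Test | r = 0.5 | r = 0.7 | r = 0.9 |
|---|---|---|---|
| Change, <150 versus 300+ | >99% | 99.6% | 72% |
| Pre-post within <150 | 99% | 89% | 44% |
| Pre-post within 300+ | 99% | 90% | 43% |

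**Step 4: less favourable assumptions** (lowest versus highest group):

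- Grouping variable correlated only 0.5 with the outcome's baseline, as could happen with minutes of exercise against all-domain MET-min: about 81% at r = 0.5, falling to about 25% at r = 0.9.
- Few women above 300 (mean 120, SD 100; 3.6% of 160, about 6 women): about 90% at r = 0.5, falling to about 31% at r = 0.9.

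**Step 5: a real, uniform gain.** Adding 60 min/week for everyone (base case, r = 0.7) gives about +111, +60 and +9 across the three groups. The gradient remains, but the most active group shows no net loss.

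**Step 6: the randomised contrast.** IN versus ON change within the lowest or highest group rejects in 4.1% to 5.6% of simulated trials (N = 160 or 200), close to the nominal 5%. Regression to the mean is the same in both arms and cancels.

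**The case against.** The strongest reply is that the faulty analysis is inferred. The subgroup sentence follows directly on sentences about IN versus ON, and in a two-arm trial a subgroup analysis ordinarily means the arm contrast by subgroup. On that reading there is no artefact. The subgroup clauses also name no outcome and no time point, and a full protocol or analysis plan may settle both.

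Part of this stands: the baseline time point, the outcome and the contrast are each partly inferred. But the sentence speaks of differences between the PA-level groups, the hypothesis concerns benefit regardless of weekly PA, and the listed tests are unadjusted and include pre-post tests. Someone following the text could run the faulty comparison and remain within the plan.

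A reader might also infer three stronger points that the article does not support:

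- *That the trial would report a loss of activity in active women.* This needs an overall gain smaller than the artefact. Step 5 shows a case without a net loss.
- *That a false positive is practically certain.* That is the upper case, with one variable for grouping and outcome, well-filled groups and moderate r.
- *That cut-offs in min/week are unusable because the outcome is in MET-min/week.* Table 2 also lists session duration and weekly frequency, so minutes per week can be derived, and nothing says the cut-offs apply to the MET score. The unit difference is minor. If grouping and outcome do use different measures, it weakens the artefact without removing it.

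**Conclusion.** The concern holds in a limited form. The plan permits comparing change in weekly PA across PA-level groups, or testing it pre-post within them, and either would show a spurious gradient favouring inactive women.

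If the programme has no effect and 160 women are analysed, the lowest-versus-highest comparison would be significant in about 70% to over 99% of trials when grouping and outcome are the same variable, and in about 25% to 90% under the weaker conditions of Step 4. The exact rate depends on an assumed PA distribution and correlation. The direction does not, and every scenario examined is far above 5%.

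The point concerns a secondary subgroup analysis of a primary outcome. The randomised IN–ON comparison, overall or within a PA group, is not affected. Fitness outcomes are touched only as far as they correlate with the error in baseline PA.

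**What to change.** Add the following to Objectives and to Statistical methods for primary and secondary outcomes:

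1. The PA-level groups are defined from baseline minutes per week, derived from the duration and frequency items already collected.
2. For PA outcomes, the groups are used only to examine the IN–ON difference within each group, through an arm-by-baseline-PA interaction adjusted for baseline PA. PA change is not compared across the groups or interpreted pre-post within them.

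This takes about two sentences and no new data. The cost is the loss of a descriptive contrast of PA change across activity levels, which could not be read as a programme effect anyway. Completion is expected in December 2026, so the wording can be settled before the final analysis.
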